## ABBREVIATIONS LIST

---

- (AFSSAPS)-DEDIM    Département d'Évaluation des Dispositifs Médicaux
- AE                    Adverse events
- AFSSAPS            Agence Française de Sécurité Sanitaire des Produits de Santé
- BP                    Blood Pressure
- CCTIRS            Comité Consultatif pour le Traitement de l'Information en matière de Recherche sur la Santé
- CF                    Cardiac Flow
- CLB                   Centre Léon Bérard
- CLM                   Colorectal Liver Metastases
- CNIL                   Commission Nationale Informatique et Liberté
- CNOR                Certified Nurse Operating Room
- CPP                   Comité de Protection des Personnes
- CRA                   Clinical Research Assistant
- CRF                   Case Report Form
- CRT                   Clinical Research Technician
- CSA                   Clinical Study Assistant
- ESI                    Experimental Surgery Institute
- HIFU                  High Intensity Focused Ultrasound
- HR                    Heart Rate
- INSERM            Institut Nationale de la Santé et de la Recherche Médicale
- MD                    Medical Device
- PaCO2                Partial pressure of Carbon dioxide in arterial blood
- PAO2                  Partial pressure of Oxygen in arterial blood
- RPC                   Regional Pharmacovigilance Centre
- RR                    Respiratory Rate
- SAE                   Severe Adverse Events
- SpO2                  Saturation of Peripheral O2
- TCIA                  Target-Controlled IntraVenous Anaesthesia
- UBET                  Unité de Biostatistique et d'Évaluation des Thérapeutiques
- VT                    Tidal Volume
- WHO                  World Health Organization

## FOREWORD

---

In this protocol the following terms will be used:

- “**Shootings**” means to deliver an ultrasound load through a HIFU transducer in order to cause a necrosis in a determined area.
- “ **Hurt**” refers to the necrosed area generated by the use of HIFU

## SYNOPSIS

---

### SHORT TITLE

---

**HIFU**

### TITLE

---

A phase I-II study to evaluate, in patients operated for a hepatic resection of colorectal liver metastases, a High Intensity Focused Ultrasound (HIFU) procedure: feasibility, safety and accuracy

### PROTOCOL NUMBER

---

N° CLB : ET2009-068

N° ID RCB : 2009-A00779-48

### SPONSOR

---

Centre Léon Bérard (CLB) - LYON

### COORDINATING CENTRE

---

Unité de Biostatistique et d'Évaluation des Thérapeutiques (UBET) – Département de Santé Publique (DSP) – CLB

### INDICATION

---

Colorectal Liver Metastases (CLM) requiring surgery.

### RATIONALE

---

In France, the ColoRectal Cancer (CRC) is the second cancer considering its incidence with about 36 000 new cases each year (source: French network of cancer registers). It still have a poor prognosis causing nearly 16 000 deaths a year and the more often due to metastases.

Hepatic resection is the mainstay for CLM and remains to date the only curative treatment. However, only few patients (10 to 20 %) can benefit from it. Consequently, many techniques were developed and evaluated, such as focused radiofrequency or cryotherapy, in order to find out an alternative to the surgery of CLM. Nevertheless, these widespread techniques have many limitations: they do not enable reliable real-time monitoring, they are invasive, can only be applied to small tumors, imply long duration treatment and lead to high rate of local recurrence.

Therefore, it is necessary to develop a more accurate process to kill tumoral cells, which would not be size-limited nor invasive, in addition to the surgical treatment.

High Intensity Focused Ultrasound (HIFU) is a new approach, which enables to generate irreversible cell death through coagulative necrosis in a few seconds. There is no cooling effect of the perfusion because of the shortness of the phenomenon. Perioperative HIFU in CLM has never been evaluated clinically. The surgical team of the Centre Léon Bérard, in collaboration with the INSERM U556 one, has undertaken a research program on CLM treatment by HIFU. A new and very powerful device, without the previously listed limitations, has been developed. Preclinical studies revealed the interest, the feasibility and the safety of this process. These results enable to consider the implementation of a clinical trial.

### STUDY DESIGN

---

Prospective, monocentric phase I/II study evaluating a surgical medical device (SMD)

### MAIN ASSESSMENT CRITERIA

---

#### **1st part;** Phase I

- ✓ (Feasibility) Ability to perform shootings, supplementary duration of intervention < 30 minutes
- ✓ (Safety) Asepsis, absence of lesion of nearby tissues.
- ✓ (Tolerance) Preservation of hemodynamic and respiratory vital signs.

#### **2nd part:** Phase IIa

- ✓ (Accuracy) distance from the epicentre of the HIFU lesion to the mark previously positioned in the liver ≤ 5mm.

#### **3rd part:** Phase IIb

- ✓ (Efficacy) macro-lesion generated, including metastasis, in negative margins.

### POPULATION

---

---

**Inclusion criteria**

- 18 years old or more patient,
- Affected of hepatic metastasis of a colorectal cancer,
- Who must undergo a hepatectomy by laparotomy with the aim of the resection of hepatic metastasis,
- ECOG performance status (PS) = 1,
- Mandatory affiliation to a health security insurance,
- Written informed consent.

**Non-inclusion criteria**

- Having already undergone a major hepatic surgery (more than three segments) or biliary major (context of major iterative hepatic surgery),
- Having already undergone a major abdominal surgery with the exception of a colorectal surgery for the treatment of its primitive tumor (the surgery of the gall-bladder by laparoscopy for the deadline upper to 6 months do not constitute a criterion of non inclusion),
- Unable to be followed during the duration of the study,
- Pregnant or breast-feeding woman (a pregnancy test must be negative at the time of the inclusion in the study for the women in age to procreate; a method of reliable contraception must be used during the duration of the study).

---

**STUDY PROCEDURE****Inclusion**

The patients will be included during the surgery preliminary visit, by the surgeon

**Surgical Procedure****✓ Settings**

During the first part of the intervention, once liver freed and indication of liver resection checked, prior to undertake any specific procedure regarding liver resection, the investigator surgeon will perform the shootings on the dedicated part of the liver.

**✓ Phase I**

The shootings will concern the healthy liver to remove, distant to the important vascular structures and metastases. Two HIFU shootings will be made on each patient: one on the surface of the liver and the other one in depth.

**✓ Phase IIa**

The shootings will concern healthy liver to remove, distant (step 1) then close (step 2) to the important vascular structures of the liver. Several shootings HIFU will be done on each patient (ideally 4 hurts, minimum 2 hurts).

**✓ Phase IIb**

Shootings will concern small liver metastases to be resected and will be juxtaposed on multiple plans, to generate a hurt containing the metastasis and guaranteeing sufficient safety margins. Several metastases can be treated in the same patient.

*NB:* After the HIFU shootings, there will be no difference regarding the hepatectomy: this one will be as identical as the one which would have been done in the absence of HIFU shootings.

**Immediate following of the operation**

The whole abdominal cavity will be explored to detect possible adverse effects.

The anatomopathological analysis will include, in addition, an analysis of each of the HIFU hurts.

**Postoperative follow-up**

Within the framework of this study, the patients will be followed during 30 days after the surgical operation.

---

**STATISTICAL METHODS**

32 to 38 patients will be included (phase I : 6 patients, phase Iia : 6 to 12 patients, phase IIb : about 20 patients).

For each phase, analyses will be achieved in the selected population to evaluate the clinical feasibility, the tolerance and the efficacy in CLM treated by HIFU. This population concerns all the patients included in the study and who underwent a hepatectomy. The data analysis will be mainly

---

descriptive.

An interim analysis will be given to the Steering committee in charge of the study.

This Committee will meet to make the necessary decisions as for the continuation of the study according to its progress, in agreement with the Sponsor.

### **Key steps identification**

---

|                                           |                                      |
|-------------------------------------------|--------------------------------------|
| Start of enrolment :               | first quarter 2010                   |
| Inclusion period :                 | 18 months                            |
| Patients follow-up :               | 30 days after the end of the surgery |
| Estimation of the study duration : | 19 months                            |

## **I. Introduction and rationale**

---

### **I.1. Surgical resection of liver metastases in colorectal cancer: current situation**

Colorectal liver metastases (CLM) are a major public health issue (16 000 deaths each year in France) (1). Despite all improvements achieved regarding chemotherapy (2) and other therapies based on the use of physical agents (radiofrequency and cryotherapy) (3;4), complete resection of CLM offers the only potential curative approach - A 5-year survival rate after liver resection is ranged from 20 to 35%. However, only few patients (10 to 20 %) can benefit from it. Mainly because of the number, the location, and the size of the liver metastases or because the insufficient remaining functional liver volume contraindicates the surgery (5;6).

Consequently, many alternatives to surgery of CLM have been evaluated. Currently, focused radiofrequency, cryotherapy, micro-waves and laser hyperthermia are the main local treatments used in CLM (7). Radiofrequency, and cryotherapy, which are more common, led to an increase of the number of patients treated for CLM with promising results. These techniques have yet several limitations. They do not enable reliable real-time monitoring (per operative treatment modification cannot be done with CT-scan) and require intraparenchymal introduction of a probe. Moreover, only small hepatic volume can be targeted. Finally, a 2-year recurrence rate is important. It ranges from 30% to 40% for cryotherapy and nearly 15% (2% -60%) for radiofrequency (8, 9).

Therefore, it is necessary to develop a more accurate process to kill tumoral cells which would not be size-limited nor invasive, in addition to surgical treatment. The main goal is to make curative surgery possible for a larger population and to reduce the rate of liver recurrences after resection. To this extent, focused tumoral treatments provide a good efficacy and spare more significantly healthy liver.

### **I.2. Therapeutical use of ultrasounds**

HIFU are mechanical waves generated by an ultrasound transducer. A focused approach enables a sudden and accurate energy absorption in a distant but precisely defined targeted area. This induces a temperature increase going from 40 to 60°C in a few seconds and generates irreversible cell death through coagulative necrosis in an ellipsoidal shape with a 15 mm long axis and a diameter of 20 mm. There is no cooling effect of the perfusion because of the shortness of the phenomenon. The main asset of the technique is the use of non-ionizing waves which allows high focusing without hazardous effects on surrounding tissues. Plus it leads to almost no adverse effects. Thus, for about two decades, therapeutical ultrasounds implementations (hyperthermia, HIFU, lithotripsy) have been rising and explored in numerous ways: extracorporeal, percutaneous, transrectal, laparoscopic, transoesophageal, perioperative. Preclinical and clinical studies using these treatments concerned various pathologies such as glaucoma (10 ;11), localized prostate carcinoma (12 ;13), benign prostate hypertrophy (14;15), or other organs like bladder (16), breast (17), oesophagus (18), liver (19), uterine fibroma (20) or even brain (21). Because of the different ways to reach organs to be treated and depending on the way chosen for the treatment, many specific transducer technologies were developed. Nowadays, therapeutic ultrasounds appear as a great supplementary option to surgery among treatments using physical agents. Despite all these elements, HIFU technologies are to be improved concerning CLM treatment. It is in particular necessary to decrease the time of intervention because the elementary hurt HIFU is ellipsoidal and of small dimensions. A treatment by HIFU consists in juxtaposing in a precise way (generally by a movement automated by the probe of treatment) these elementary hurts until containing the tumor targeted with a margin of healthy tissues.

At the present time a treatment of prostate cancer by HIFU takes 149 minutes (22). Moreover, a real-time imaging device must be combined to HIFU to see precisely the treated area after each shooting.

Extracorporeal treatments in primitive liver cancer using HIFU are currently tested by Chinese and English teams but come up with questions that are not yet answered: bones stopping waves propagation, air filled spaces and targeting difficulty related to breathing. Furthermore, it is hard to reach liver in depth.

For all these reasons the surgical team of the CLB, in collaboration with the NIHMR U556 one, has undertaken a preclinical research program on CLM treatment by HIFU. A new and very powerful device enabling large hurts in the liver, has been developed.

### I.3. Development of a toric hifu transducer for treatment of CLM

Cf. biblio (23;24)

[figure not shown]

Figure 1 : HIFU probe.

A perioperative ultrasound medical probe in treatment of CLM with HIFU has been developed and received at a preclinical phase in a porcine model. 7 cm^3 large (20 mm of diameter and 25 mm of long axis) unitary conical resections were done in 40 seconds with a crossed toric transducer which is an efficient result considering the time consumed and the volume treated. A hole in the middle of the medical device (MD) enables to add an echographic probe to localize and control liver metastases treatment. Characteristics of the generated hurts were studied on the models and in *in vitro* and *in vivo* preclinical studies.

#### I.3.a. Preclinical study of HIFU treatment feasibility: analysis of a single hurt and strategies to extend necrosis

Cf. biblio (25;26)

[figure not shown]

Figure 2: (a) Elementary HIFU hurt generated in 40 seconds  
(b) Echographic aspect of elementary HIFU hurt.

One of the most important things, concerning the CLM treatment, is the accuracy of targeting. In standard surgery or with a therapy using physical agents (radiofrequency, cryotherapy) the treatment is considered properly done when a tumor is killed with negative geometrical margins. The elementary hurt generated by the toric HIFU transducer in treatment of CLM was thoroughly studied in preclinical phase *in vivo* in pig liver. Its geometrical features (Figure 2a) and the absence of cooling effect on perfusion are really relevant to cure CLM taking into account its rich vascularization. The perioperative manual use of toric HIFU transducer prototype gave accurate localized treatment in liver, thanks to the echographic guidance provided by the combined probe. Since both localization and necrosis in liver tissues were controlled, the proposed HIFU treatment seemed to be more convenient. The hurts are homogenous and have, microscopically or macroscopically, well defined borders.

Generated hurts are easily visible on echographic pictures (Figure 2b) which makes possible to place side by side several elementary cone-shaped hurts to extend the size of the generated necrosis (Figure 3). The treatment is non-invasive to the organ and is well tolerated.

[figure not shown]

Figure 3: Juxtaposition of 6 elementary hurts

### 1.3. b. Preclinical study of HIFU treatments efficacy with a pseudotumoral pattern

Cf. biblio (27)

[figure not shown]

Figure 4 : PseudoTumor HIFU

The objective of these studies was the preclinical evaluation of the accuracy of the toric HIFU transducer prototype in treatment of CLM, using a pseudotumoral pattern implanted in a pig liver. This pattern is identifiable in both anathomopathology and echographic imaging, and can therefore estimate the accuracy of the volume targeted by HIFU (Figure 4). Hurts were done ensuring negative margin all around the pseudotumor and in all directions.

Studied shootings on a pseudotumoral pattern measured precisely the accuracy of the treatment using juxtaposed elementary hurts to generate large and well targeted liver lesions. Through all these

preclinical studies, clearly appears the interest of using a HIFU transducer manually in a perioperative procedure.

### **I.3.c. Collaboration with the EDAP society – Development of a perioperative usable prototype in human being**

Previously described studies were undertaken with experimental prototype developed by the unit 556 of INSERM in collaboration with the EDAP society which has the world leadership in HIFU prostate cancer treatment. In this indication, was developed Ablatherm® which is now worldwide spread. The work previously described was funded through a research program “Preuve de Concept” proposed by the “Canceropôle Lyon Auvergne Rhône-Alpes” (CLARA). Positive results led EDAP society, with the help of “Oséo-ANVAR”, to create a new MD usable in human being: MFOCUS® prototype

### **I.4. Experience of the team in this subject**

The CLB surgical team’s proficiency in curing liver metastases, especially CLM, is well known. This is shown by an important activity of liver metastases resections (80 to 100 operations/year), by the development of focused technologies to kill tumors in addition to or as an option to surgery, by the involvement in a large number of clinical trials with frequent collaborations with medical oncology teams (28)

For 3 years since then, in collaboration with the U556 of INSERM, a research program has been developed on HIFU as treatment of CLM (24). The experience gathered through *in vitro* and *in vivo* preclinical experimentations found in national and international publications makes it today possible to conceive a rigorously led study to evaluate the feasibility, tolerance and efficacy of this technique.

**Thanks to those results and the support provided by contributors, a clinical trial using this new therapeutic procedure is now conceivable in order to evaluate its performances in liver metastases treatment, which is the main point of the protocol.**

**It will be the first time in human being, and the first time in the whole world that a perioperative HIFU technique is assessed in treatment of liver metastases in addition to surgery.**

## **II. Overview of the study**

---

### **II.1. Treatment indication**

Treatment of CLM.

### **II.2. Study design**

This is a phase I/II, prospective, monocentric (CLB), first time evaluation in human being of a surgical MD without CE mark.

### **II.3. Benefit / risk ratio**

The principal objective of the study is to confirm the results given in the pig model in human liver. It is important to remind that former experiments were well tolerated.

The study participants cannot expect any personal benefit from their participation.

However, to avoid any problem, it has been decided to test it in patient undergoing a curative operation for CLM. The surgical procedure to cure these patients' candidates to a liver resection will be totally identical to the one they would have undergone if not included in the study. The only difference will concern HIFU shootings on the healthy or peritumoral liver (depending on the study phase). These shootings will be performed, on liver to be resected, only after ultimate checking of indication and immediately before the resection phase. Thus, there is no risk to generate HIFU hurts on a healthy liver part that would not have to be resected.

The duration of the procedure of HIFU shootings will have to prolong the surgical operation of no more than 30 minutes. (Phase I main assessment criteria).

The principal potential risk to which could be exposed the patients of the study would be a hurt of surrounding organs secondary to HIFU shootings. This risk will be, of course, estimated after each shooting and this all through the study. Safety measure will be taken with particular care to avoid any accident: compresses will be put under the targeted area to limit risks of ultrasound propagation, and the shootings axis will not point towards noble intra-abdominal organs.

The post operative follow-up period will last 30 days, which seems to be enough time to report possible late AE. In that case, total care will be given until total remission or at least stabilization of adverse events.

Besides, the patients' enrolment will be divided into steps including from 2 to 4 participants (depending on the study phase). The decision to proceed to next steps will be taken by an independent Steering committee after considering all the study results. Naturally, the study could end prematurely due to SAE or accident.

Generally speaking, if the results of this study appear to be clinically relevant, the development of this technique could be a huge improvement in treatment of CLM, by providing non-invasive surgery for the considered organ and to extend this treatment to other patients who cannot benefit from hepatectomy (too large liver volume to resect, metastases localization, etc) or developing new extracorporeal treatment processes...

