#### VI.1.a. Phase I

**A group of 6 patients** will be included, in a sequential analysis divided into 2 steps following Lee's criteria (29). This analysis aims to stop prematurely the study if a failure rate  $> 15\%$  is observed.

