#### VI.1.b. Phase II

##### ✓ Phase IIa

**A group of 6 to 12 patients** will be included in 2 sequential steps with 3 to 6 patients in each. This number of selected patients has been defined by a classic dose escalation method used in clinical trials. The goal is to bring to light an insufficient accuracy of HIFU shootings if this event arises with a high frequency. Based on the binomial distribution, groups of respectively 3 and 6 patients allow a  $90\%$  probability to get at least one patient receiving an unacceptable shooting (inaccuracy), if this event occurs respectively in at least  $54\%$  and  $32\%$  of the cases.

[figure not shown]

• **1st step** (3 to 6 patients) :

A success is defined for one patient in a given amount of shootings ( $2 \leq n \leq 4$ ), if the mean distance between the closest hurt limit to the mark and the mark itself is  $< 5$  mm. Otherwise, the event will be considered as a failure.

3 patients will be included in the 1st step:

- If no failure is noticed → proceed to step 2;
- If 1 or 2 failure is(are) noticed 3 more patient are included in first step.
  - ↳ If  $> 2$  failures out of 6 → the study is stopped,
  - ↳ If  $\leq 2$  failures out of 6 patients → proceed to 2nd step
- If 3 failures are noticed → the study is stopped.

[figure not shown]

• **2nd Step** (3 to 6 patients) :

A success is defined for one patient in a given amount of shootings ( $2 \leq n \leq 4$ ), if the mean distance between the closest hurt limit to the vessel mark and the vessel it-self is  $\geq 5$  mm and  $< 10$  mm. Otherwise, the event will be considered as a failure.

3 patients will be included in the 1st step:

- If no failure is noticed → proceed to phase IIb;
- If 1 or 2 failure is(are) noticed, 3 more patient are included in first.
  - ↳ If  $> 2$  failures out of 6 → the study is stopped,
  - ↳ If  $\leq 2$  failures out of 6 patients → proceed to phase IIb,
- If 3 failures are noticed → the study is stopped.

NB: At the conclusion of the phase IIa, the Steering committee of the study will meet to examine all the brought together data, validate or not the criteria of continuation of the study and define more exactly the methodology of the phase IIb.

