## ✓ **Phase IIb**

[figure not shown]

A group of 20 patients will be included in this phase. This number has been defined as following:

- The statistical unit for analysis is the metastasis,
- Fleming-A'Hern's method was formerly developed for phase II studies without steps (30) and has been used to determine the number of metastasis to target. A success is defined by a hurt encompassing the metastasis and guaranteeing safety margin  $\geq 5$  mm from any point, within a maximum of 15 shots.

The next hypotheses are used, in which P is the success probability:

- $p_0 = 0,70$  is the superior limit value of success rate which, if met, would mean that HIFU are inefficient on metastases to be resected and peri lesional healthy liver.
- $p_1 = 0,90$  is the inferior limit value of success rate which, if met, would mean that HIFU are efficient to treat metastases to be resected and peri lesional healthy liver.

Given a 5 % alpha risk and an 80 % statistical power, 28 metastases will have to be targeted by HIFU to conclude unilaterally. Assuming that about 1,5 metastases will be targeted on each included patient, that is to say nearly 20 patients.

A count of successes  $\geq 24$  enables to reject  $H_0$  in favour of  $H_1$ .

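### Section II.3 offers small enrolment steps with a committee decision as a protection for the whole study, but the phase IIb text writes no step or scheduled safety decision for its 20 patients

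*Protocol*

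**What the plan says.** Section II.3 makes the benefit/risk case for a first use in humans of a device without CE mark. It names the main hazard: "The principal potential risk to which could be exposed the patients of the study would be a hurt of surrounding organs secondary to HIFU shootings". Among the protections it lists, it states that "enrolment will be divided into steps including from 2 to 4 participants (depending on the study phase"), and adds: "The decision to proceed to next steps will be taken by an independent Steering committee after considering all the study results". The words in parentheses let the step size vary by phase; they exempt no phase.

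Section VI then sets the rules phase by phase.

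- **Phase I (VI.1.a):** six patients "in a sequential analysis divided into 2 steps", 2 and then 4. Accidental injury to a neighbouring organ is one of the failure criteria.
- **Phase IIa (VI.1.b):** the patients "will be included in 2 sequential steps with 3 to 6 patients in each". Each step opens with 3 patients and takes 3 more if 1 or 2 failures are seen. Failure is defined by distance only.
- **Phase IIb (VI.1.b):** "A group of 20 patients will be included in this phase". The sizing method, Fleming-A'Hern, "was formerly developed for phase II studies without steps (30) and has been used to determine the number of metastasis to target". Success means that the lesion covers the metastasis with the required margin "within a maximum of 15 shots". There is one decision, at 24 or more successes.

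**The concern.** Stepwise enrolment is part of the argument that the risk to participants is acceptable, and II.3 also says that they can expect no personal benefit. The phase without written steps has the most patients. It also allows the most shots per patient: up to 15 per metastasis, with several metastases per patient permitted, against 2 shots in phase I and 2 to 4 in IIa.

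Organ injury is a stopping criterion in phase I only. In IIa and IIb it is a secondary safety objective that enters no decision rule. An injury that does not qualify as a severe adverse event is entered in the case report form, because V.1.b requires immediate notification only for severe events. In phase IIb, no scheduled point then brings such an injury to the committee before the next patients are treated.

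**Working it through.** **1. The efficacy design reproduces and is not in question.** Inputs from VI.1.b: p0 = 0.70, p1 = 0.90, one-sided alpha 5%, power 80%. With X binomial on n = 28, each metastasis an independent unit:

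- P(X ≥ 24 | 0.70) = 0.047
- P(X ≥ 24 | 0.90) = 0.858

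An exact search from n = 15 upwards finds 28 to be the smallest number that meets both limits. At 1.5 metastases per patient, 28 / 1.5 = 18.7, which the protocol takes as about 20 patients.

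**2. Written increments against II.3 (2 to 4 per step).**

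| Phase | Written increments | Within 2 to 4? | Organ injury in the decision rule? |
|---|---|---|---|
| I | 2, then 4 | yes | yes |
| IIa | 3, then 3 if needed, in each of two steps | yes | no |
| IIb | 20 | no | no |

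**3. What II.3 would mean for phase IIb.** Steps of 4: 20 / 4 = 5 steps, so 4 decisions before the last step. Steps of 2: 20 / 2 = 10 steps, so 9 decisions. The visible phase IIb text has none.

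**4. Share of the study.** Patients: 20 / 38 = 53% to 20 / 32 = 63%. Shots in phase I: 6 × 2 = 12. Shots in IIa: 6 × 2 = 12 to 12 × 4 = 48. Phase IIb has an upper bound, if every one of the 28 metastases needed the full allowance, of 28 × 15 = 420. The protocol gives no expected number of shots per metastasis, so 420 is a ceiling and not a forecast.

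**5. What the earlier phases could show.** Before phase IIb, 6 + 6 = 12 to 6 + 12 = 18 patients will have been treated. If none had an organ injury, the one-sided 95% upper limit for the rate per patient would be 1 − 0.05^(1/12) = 22% to 1 − 0.05^(1/18) = 15%, at 2 to 4 shots per patient. A clean record would not make safety review in phase IIb redundant.

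**6. Effect of safety-only steps on the test.** Success would be declared only if the phase is completed and X ≥ 24. That probability cannot exceed P(X ≥ 24), so under p0 it stays at or below 0.047. A safety stop can only lower the chance of declaring success.

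**The case against.** The case for leaving the text alone has real weight.

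- **Wording.** The phrase about studies without steps describes where the sizing method comes from. It is not an enrolment rule. Phases I and IIa are also introduced as a group and are then split. A reader might infer that the phase IIb text forbids steps; it does not.
- **Missing figures.** The figures at the phase IIb design and objectives are not shown and might contain an enrolment scheme. The point therefore rests on the visible text.
- **Provisional design.** The committee meets after IIa and may refine the phase IIb methodology, so steps could still be added.
- **Existing oversight.** A reader might infer that phase IIb runs unsupervised. It does not. Risk is assessed after each shot, and II.3 allows a stop for a severe event or an accident. The abdomen is explored for burns in every operation (IV.2.c), severe events are notified at once (V.1.b), the study may end early on benefit/risk grounds (IV.5), and the committee has a continuation role without set times (VIII.1). In a single-centre trial the surgical team sees a burn immediately.
- **Loose summary.** II.3 is not followed to the letter elsewhere either. The committee's consent is named at the end of phase I and its meeting at the end of IIa, but not at every increment. It would be wrong to say that phases I and IIa have a committee decision every 2 to 4 patients.

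All of this stands, and it limits the point. It does not close the gap: none of these provisions is enrolment in small steps with a decision between them, which II.3 presents as already part of the plan. The possible later refinement fixes nothing now.

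**Conclusion.** The point holds as a mismatch between a stated safeguard and the rules that should deliver it. II.3 covers the whole study. The visible phase IIb text provides neither step nor scheduled safety decision for 20 of 32 to 38 patients, and the IIa and IIb rules leave out the risk that II.3 ranks first. It should be corrected before phase IIb opens, but it is no flaw in the sample size or the efficacy test, whose stated alpha and power are met.

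One might also be tempted to put a number on the injuries that steps would prevent. The protocol gives no rate of organ injury. Its failure and inaccuracy percentages (15% in phase I, 54% and 32% in IIa) measure other things, and any such count would assume that nobody used the accident stop. No such figure is offered here. The conclusion assumes that the figures not shown contain no phase IIb steps, and that the II.3 sentence means what it says for all phases.

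**What to change.** In VI.1.b, Phase IIb:

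1. Keep the single-stage test (28 metastases, 24 or more successes).
2. Add enrolment steps of at most 4 patients. Before each next step the Steering committee reviews perioperative organ-injury findings and severe events to date. It does not see the success count and does not wait for the full 30-day follow-up.
3. State that any accidental injury to a neighbouring organ in IIa or IIb holds inclusion until the committee has reviewed it. Lesions of the Glisson capsule on the entrance side are excepted, as the protocol already accepts them.

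The hold goes beyond what II.3 promises. It is proposed because the IIa and IIb rules do not count this event. The IIa accuracy rules stay unchanged.

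If steps are not wanted in phase IIb, limit the II.3 sentence to phases I and IIa and keep the hold.

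**Cost.** Amendment wording and no new data: burns are looked for in every operation (IV.2.c) and organ injury is recorded in all phases (IV.3.a). Planned accrual is 32 / 18 = 1.8 to 38 / 18 = 2.1 patients per month, so steps of 4 mean a review about every two months and a pause of days each time. Waiting for 30-day follow-up at each of the 4 reviews would add about 4 months, which is why that is not advised.
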